### Objectives

2.1

The primary objective is to assess whether different Rapamycin doses increase Treg number in ALS patients compared with the control arm.

Secondary objectives include the following:

1.*Assessment of Rapamycin safety and tolerability in a cohort of ALS patients*: occurrence of adverse events (AEs), changes on clinical examination including vital signs and weight, and laboratory examinations (biochemistry, hematology and urinalysis) will be registered throughout the entire study duration.2.*Biological assessment*: To analyze Rapamycin efficacy in inhibiting MTOR pathway, by quantifying the phosphorylation of the S6 ribosomal protein (S6RP) comparing baseline and weeks 8, 18 (treatment end), 30, and 54 between Rapamycin arms and placebo arm. To identify changes in activation and homing capabilities of different T, B, NK cell subpopulations comparing baseline and weeks 8, 18 (treatment end), 30, and 54 between Rapamycin arms and placebo arm. To study Rapamycin effects on different biomarkers (including peripheral and CSF biomarkers, that is, creatinine and albumin, CK, vitamin D, plasma/CSF neurofilament heavy/light chain protein) comparing baseline and week 8, 18 (treatment end), 30, and 54 between Rapamycin arms and placebo arm. To identify Rapamycin-induced changes in inflammatory status, by the molecular analysis of the inflammasome system baseline and week 8, 18 (treatment end), 30, and 54 between Rapamycin arms and placebo arm. To assess Rapamycin capacity to pass through blood–brain barrier (BBB).3.*Clinical assessment*: to assess changes in Amyotrophic Lateral Sclerosis Functional Rating Scale (ALSFRS)-Revised from baseline to weeks 4, 8, 12, 18, 30, 42, and 54 in placebo and treatment arms; overall survival from randomization to date of documented death or tracheostomy; survival rate at weeks 18, 30, 42, and 54; forced vital capacity (FVC) score from baseline to weeks 4, 8, 12, 18, 30, 42, and 54.4.Quality of life assessment: ALSAQ-40 from baseline to weeks 8, 18, 30, and 54 in treatment and placebo arms.

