### Treatment and blindness

2.7

This study is a phase II randomized, double-blind, placebo-controlled, multicenter, clinical trial (RCT) to test Rapamycin in ALS patients. The study will include 63 ALS patients (EL Escorial Revised Criteria, sporadic and familial) with 1:1:1 allocation in 3 groups of 21 subjects each; treatment will be double blinded, and will last 18 weeks. Active treatment will include oral Rapamycin at 1 mg/m^2^/d or 2 mg/m^2^/d.

Rapamycin levels will be regularly measured and revealed only to an independent monitor, who will input Rapamycin levels on a separate eCRF, and on the basis of that value dosing changes may be performed at each treatment dispensation directly through eCRF (and blinded to caring neurologists who will supply bottles identified by a number and corresponding to different blinded doses) to keep Rapamycin levels from 4 to 12 ng/mL. Computerized randomization will be stratified by ΔFS (</≥0.7).

After treatment end (week 18) patients will be followed up for further 36 weeks. This large period of follow-up has the aim to assess potential late side effects of the treatment and to assess whether eventual biological or clinical effects of the treatment with respect to placebo, may last after drug discontinuation.

For the first 10 patients enrolled, clinical and biological safety assessments will be performed every week for the first month, and then every 2 weeks until the end of treatment. For the remaining 53 patients clinical assessments will be performed every 2 weeks for the first month, and then every 4 weeks during treatment duration.

If at either the interim or the final analyses safety concerns will arise, the trial will be stopped and all available data will be reviewed by the Study Steering Committee.

Table 2 shows study procedures to be undertaken.

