### Sample size calculation

2.13

The sample size has been estimated considering as the primary outcome measure the proportion of positive response (Tregs number increase) at treatment end (18 weeks) in patients treated with Rapamycin versus placebo.

ALS patients have a slight reduction of Treg% (mean±SD: 2.1 ± 0.7) with respect to healthy controls (2.6 ± 0.6) (Treg% calculated on total lymphocytes; normal values of total lymphocytes: 1000–4500/μL; normal values of total Treg: 71.5 ± 17/μL).^[22]^

Slowly progressive ALS patients have a number of Tregs that is equal to healthy controls, whereas fast progressors have 31% fewer Tregs than slowly progressing patients, and Treg % is inversely correlated with the rate of disease progression.^[8]^ These data indicate that ALS patients have 60 ± 17 Treg/μL (fast progressors: 49.3 Treg/μL; slow progressors: 71.5 Treg/μL). As a result, a “positive response” can be considered an increase of the proportion of Tregs by ≥30%. The null hypothesis is that Rapamycin does not increase significantly the proportion of positive responses in treated patients at 18 weeks compared with their baseline stage and to placebo group. The alternative hypothesis is that Rapamycin determines a proportion of positive responses in ≥50% of treated patients compared with a maximum 5% of patients in the placebo group. The study has been designed to reject the null hypothesis with an alpha error of 0.025 (to take into account a multiple comparison with a control arm) and a power of 0.80. For this purpose, a sample of 54 patients randomized in 3 treatment arms would be needed. Considering an average drop out of 15% then a recruitment of 63 patients will be necessary.

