### Statistical analyses

2.14

Separate analyses will be performed in

1.all randomized subjects receiving ≥1 dose of study medication (intention-to-treat population);2.all randomized subjects excluding protocol deviations (per protocol, PP population).

Descriptive statistics will be performed comparing the 2 groups of Rapamycin treatment and placebo. Continuous variables will be described using mean and standard deviation or median and interquartile range; categorical variables will be described as counts and percentages.

Safety analysis will be performed in all subjects receiving ≥1 dose of the experimental drug. All AEs, SAEs, and AEs leading to treatment discontinuation will be recorded according to ICH Guidelines, listed, and compared in the treatment arms at any follow-up visit and at the end of the study.

Differences in tracheostomy-free survival (Kaplan–Meier method) between the treated groups and placebo group will be compared using the log-rank test. Cox's proportional hazard model would be used to adjust for any possible unbalanced prognostic factors. Statistical significance will be set at .05 level for a 2-tailed test. Missing data will be handled using the last observation carried forward.

Immune response to Rapamycin will be analyzed as the difference in positive response to Rapamycin (mean Tregs increase >30%) between the placebo group and the Rapamycin groups. This will be calculated with the use of Treg data obtained at baseline and at week 18.

We will compare the mean values of S6RP phosphorylation, of different T, B, NK cell subpopulations, of biomarkers, inflammasome, cytokines, comparing baseline and treatment end (18 weeks) between Rapamycin and placebo arm. Mean differences in plasma concentrations from baseline to week 18 in the 2 treatment arms will be calculated and compared using *t* test or Wilcoxon–Mann–Whitney test.

The mean change over time for the same variables as above will be assessed using repeated measures ANOVA, with treatment as between-subjects factor and time as within-subjects factor. Different models will be used, each with a different biomarker of activity as the dependent variable. Models will be adjusted for any unbalanced distribution of the main prognostic factors (e.g., age) between the 2 treatment arms.

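### Alpha is split equally (0.025 per dose) for two placebo comparisons and no testing procedure is named; Holm's procedure would gain power at the same familywise error with no added patients

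*Protocol article*

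**What the plan says.** Section 2.1 (Objectives) sets the primary objective: to "assess whether different Rapamycin doses increase Treg number in ALS patients compared with the control arm". Two doses are each compared with one shared placebo arm, "with 1:1:1 allocation in 3 groups of 21 subjects each" (section 2.7).

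Section 2.13 (Sample size calculation) designs the trial "with an alpha error of 0.025 (to take into account a multiple comparison with a control arm) and a power of 0.80". The alternative is a "proportion of positive responses in ≥50% of treated patients compared with a maximum 5% of patients in the placebo group". The result is that "a sample of 54 patients randomized in 3 treatment arms would be needed", and then: "Considering an average drop out of 15% then a recruitment of 63 patients will be necessary".

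Section 2.14 (Statistical analyses) describes the primary immune analysis as a difference in responders between placebo and the Rapamycin groups from baseline and week 18 data. It names neither the test for that comparison nor a multiplicity procedure. Its only statement on level is general: "Statistical significance will be set at .05 level for a 2-tailed test".

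**The concern.** The 0.025 in section 2.13 is the article's only device against multiplicity. Carried into the analysis as it stands, it is plain Bonferroni: each dose must reach 0.025 whatever the other dose shows.

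Holm's procedure compares the smaller p-value with 0.025 and, if that is significant, the larger with 0.05. Given valid p-values, it controls the same familywise error under any dependence, including the correlation from the shared placebo arm. It needs no assumption about dose order, and it never rejects less than Bonferroni.

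The stake is the verdict on the second dose once the first has succeeded. The objective asks about different doses, only 18 evaluable patients per arm are planned, and the Discussion says that the size of the Treg increase in ALS is unknown and that this trial should inform a following one.

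**Working it through.** **Inputs (section 2.13 unless stated).** Responders 0.50 on Rapamycin (taken as equal for the two doses) and 0.05 on placebo; alpha 0.025 per comparison; power 0.80; 54 evaluable, so 54/3 = 18 per arm; 63 recruited, so 21 per arm (section 2.7). Two-sided testing is taken from section 2.14.

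**1. Reproduce the sample size.** The usual formula for two proportions, without continuity correction, is

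n = [z(1-α/2)·√(2·p̄(1-p̄)) + z(power)·√(p0(1-p0) + p1(1-p1))]² / (p1-p0)²

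with p̄ = (0.05+0.50)/2 = 0.275, √(2×0.275×0.725) = 0.6315 and √(0.0475+0.25) = 0.5454.

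n = (2.2414×0.6315 + 0.8416×0.5454)² / 0.45² = (1.4154+0.4590)² / 0.2025 = 17.35, rounded up to 18 per arm, or 54 in total. This matches the stated figure. A one-sided 0.025 would give 15 per arm. The plan therefore used two-sided 0.025 for each comparison, with 0.80 as power per comparison. For dropout, 54/0.85 = 63.5, so the stated 63 agrees within rounding.

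**2. Per-dose power at n = 18 by the same formula.**
- At 0.025: (√18×0.45 − 1.4154)/0.5454 = (1.9092−1.4154)/0.5454 = 0.905, power 81.7%.
- At 0.05: (1.9092 − 1.9600×0.6315)/0.5454 = 1.231, power 89.1%.

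**3. Power to show both doses by the normal formula.** The shared placebo arm gives correlation 0.0475/(0.0475+0.25) = 0.16. Let R(a,b) be the bivariate normal probability that both tests exceed their limits.
- Equal split: R(0.905, 0.905) = 68.0%.
- Holm: 2·R(0.905, 1.231) − R(0.905, 0.905) = 2×73.7% − 68.0% = 79.4%.

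**4. Exact enumeration of the three binomial arms.** 18 per arm, 50/50/5%, two-sided p-values, counting rejections in favour of Rapamycin:

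| Test | Both doses: split → Holm | Per dose: split → Holm | At least one dose (either procedure) |
|---|---|---|---|
| Fisher | 60.8% → 73.1% | 74.5% → 80.7% | 88.2% |
| Boschloo | 72.0% → 83.2% | 83.1% → 88.7% | 94.2% |
| Pearson z | 74.5% → 84.2% | 84.4% → 89.3% | 94.3% |
| Normal formula (steps 2-3) | 68.0% → 79.4% | 81.7% → 87.4% | 95.5% |

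With equal doses, the per-dose gain must be half the both-dose gain. For Boschloo, 83.1 + (83.2−72.0)/2 = 88.7. The last column is 2×(per dose) − (both) under the split; for Boschloo, 2×83.1 − 72.0 = 94.2. Holm leaves it unchanged because its first step is the same 0.025.

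**5. Sensitivity.**
- Doses at 50% and 40% (Boschloo): power for the weaker dose rises from 60.1% to 71.9%. With the weaker dose at 30%, it rises from 30.1% to 44.8%.
- All 21 per arm evaluable: both doses 78.5% → 87.3% (normal formula), 84.9% → 91.5% (Pearson) and 74.7% → 83.9% (Fisher). The gain is then about 7 to 9 points.

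**6. Validity of the p-values.** Holm's guarantee needs each test to hold its level. At 18 per arm the uncorrected z test at nominal 5% can reach about 6.5% at mid-range response rates, although it is far below 5% when the rate is 5%. Fisher's test stays below 3% throughout. Boschloo's test is valid by construction and less conservative than Fisher's.

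**The case against.** The strongest objection is that fixed Bonferroni testing is an inference. The 0.025 is a design input, and a trial that will use Holm can properly be sized the same way, since Holm's first step is at 0.025. Section 2.14 names no procedure, and a fuller analysis plan, which is not shown, may already specify one. This stands, so the point is conditional on 0.025 being applied to each dose in the analysis. A reader might infer that the protocol commits itself to Bonferroni; the text does not say so. Read literally, the general .05 in section 2.14 would test each dose at .05. No power would then be lost, but the correction that section 2.13 was sized for would be gone.

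Second, Bonferroni is valid and the sample size is right. That stands in full: no error-rate or sample-size defect is shown.

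Third, no section makes success of both doses a goal, and one positive dose would show target engagement. This too stands. The both-dose figure illustrates the gain and is not a shortfall against a stated target. The per-dose gain of 5 to 6 points bears more directly on the objective.

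Fourth, a reader might take one pair such as 72% to 83% as the trial's power. That pair belongs to Boschloo's test with both doses at 50%. The protocol names no test for this comparison, so a range is the honest statement.

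**Conclusion.** The point holds as an efficiency improvement. If each dose is held to 0.025 in the analysis, Holm's procedure keeps the 5% familywise error, needs no added patients and dominates the equal split. At 18 per arm, with both doses at 50% and placebo at 5%, it adds about 10 to 12 points to the chance of showing both doses and about 5 to 6 points per dose. It adds nothing to the chance of at least one success.

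The levels depend on the test and on the assumed response rates; that Holm never loses power against the split does not. The documents do not support calling the present split an error, or calling the trial underpowered against its own stated design.

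One further limit concerns the stated 0.80. As power per dose at 0.025 and 18 per arm it holds for Boschloo (83.1%) and for the normal formula (81.7%), but not for Fisher (74.5%).

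**What to change.** State in sections 2.13 and 2.14, before unblinding, that the two primary dose-placebo responder comparisons use Holm's procedure at two-sided familywise 0.05: the smaller p-value against 0.025 and, only if significant, the other against 0.05. Name a valid test for the p-values, such as Boschloo's. Make clear that the general .05 in section 2.14 is the familywise level for this pair of comparisons, so that the two sections agree.

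Keep 54 evaluable and 63 recruited. Describe 0.80 as the power per dose at the first Holm step under the chosen test; this wording would not be correct with Fisher's test at 18 per arm.

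The cost is a sentence or two of text and no patients. The one real downside is that simultaneous confidence intervals matching Holm's decisions are less simple than Bonferroni intervals.

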### Statistical analyses

2.14

Separate analyses will be performed in

1.all randomized subjects receiving ≥1 dose of study medication (intention-to-treat population);2.all randomized subjects excluding protocol deviations (per protocol, PP population).

Descriptive statistics will be performed comparing the 2 groups of Rapamycin treatment and placebo. Continuous variables will be described using mean and standard deviation or median and interquartile range; categorical variables will be described as counts and percentages.

Safety analysis will be performed in all subjects receiving ≥1 dose of the experimental drug. All AEs, SAEs, and AEs leading to treatment discontinuation will be recorded according to ICH Guidelines, listed, and compared in the treatment arms at any follow-up visit and at the end of the study.

Differences in tracheostomy-free survival (Kaplan–Meier method) between the treated groups and placebo group will be compared using the log-rank test. Cox's proportional hazard model would be used to adjust for any possible unbalanced prognostic factors. Statistical significance will be set at .05 level for a 2-tailed test. Missing data will be handled using the last observation carried forward.

Immune response to Rapamycin will be analyzed as the difference in positive response to Rapamycin (mean Tregs increase >30%) between the placebo group and the Rapamycin groups. This will be calculated with the use of Treg data obtained at baseline and at week 18.

We will compare the mean values of S6RP phosphorylation, of different T, B, NK cell subpopulations, of biomarkers, inflammasome, cytokines, comparing baseline and treatment end (18 weeks) between Rapamycin and placebo arm. Mean differences in plasma concentrations from baseline to week 18 in the 2 treatment arms will be calculated and compared using *t* test or Wilcoxon–Mann–Whitney test.

The mean change over time for the same variables as above will be assessed using repeated measures ANOVA, with treatment as between-subjects factor and time as within-subjects factor. Different models will be used, each with a different biomarker of activity as the dependent variable. Models will be adjusted for any unbalanced distribution of the main prognostic factors (e.g., age) between the 2 treatment arms.

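### Last observation carried forward, the only missing-data rule, tilts the off-drug question at weeks 30 and 54 toward a lasting effect and freezes ALS decline

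*Protocol article*

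**What the plan says.** Section 2.14 states: "Missing data will be handled using the last observation carried forward". The sentence follows the survival methods but is not confined to any endpoint, visit or reason for missingness. No other method and no sensitivity analysis is given. The same section takes Treg response from baseline and week 18, compares markers at week 18 by t test or Wilcoxon–Mann–Whitney test, and models markers over time by repeated measures ANOVA.

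Section 2.9 lists S6RP phosphorylation, cell subpopulations, biomarkers and inflammasome at weeks 8, 18, 30 and 54, and follows ALSFRS-R, FVC and ALSAQ-40 to week 54.

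Section 2.7 sets 18 weeks of treatment and 36 weeks of follow-up. One aim of the follow-up is "to assess whether eventual biological or clinical effects of the treatment with respect to placebo, may last after drug discontinuation".

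Section 2.13 plans on a "proportion of positive responses in ≥50% of treated patients compared with a maximum 5% of patients in the placebo group", says that "a sample of 54 patients randomized in 3 treatment arms would be needed", and adds: "Considering an average drop out of 15% then a recruitment of 63 patients will be necessary".

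**The concern.** Carrying a value forward assumes that the patient would have stayed where last seen. Here that assumption fails in two known ways.

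- The drug stops at week 18. A value taken on drug is not an estimate of a value off drug, yet the rule enters it as one. The follow-up exists in part to tell these two apart.
- ALS progresses. A score frozen at the last visit is better than the score the patient would have had, and a patient who has died has no score at all.

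The carried values also enter the repeated measures ANOVA as if they had been observed, so the analysis claims more information than was collected. At stake are the answer on persistence and the clinical scales that would inform a later trial.

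**Working it through.** **1. The plan's own figure.** Inputs from Section 2.13: 50% v 5%, and "alpha error of 0.025 (to take into account a multiple comparison with a control arm) and a power of 0.80". The two-sided form is taken from Section 2.14 ("Statistical significance will be set at .05 level for a 2-tailed test"). With p̄ = 0.275, the pooled formula without continuity correction gives

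n per arm = [2.241 × √(2 × 0.275 × 0.725) + 0.842 × √(0.25 + 0.0475)]² / 0.45² = 1.874² / 0.2025 = 17.35, so 18 per arm and 54 in total.

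This matches the plan. For dropout, 54 × 1.15 = 62.1 gives 63, and 54 / 0.85 = 63.5 gives 64, so the stated 63 is within one patient. The 15% belongs to a sample sized for response at week 18. It is not a loss rate for weeks 18 to 54, and the article gives none.

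**2. What is carried, by time of leaving** (markers sampled at weeks 8, 18, 30 and 54):

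| Patient leaves | Entered at week 30 | Entered at week 54 |
|---|---|---|
| before week 8 | baseline | baseline |
| weeks 8 to 18 | week 8, on drug | week 8, on drug |
| weeks 18 to 30 | week 18, end of treatment | week 18, end of treatment |
| weeks 30 to 54 | own week 30 value | week 30, off drug |

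**3. Persistence, upper case.** Assume that true off-drug response is 5% in both arms and that a share m of the active arm leaves between weeks 18 and 30, carrying the planned 50%. Then

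reported active rate = m × 50% + (1 − m) × 5% = 5% + m × 45 points, against 5% on placebo.

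| m (assumed) | Active arm | False difference |
|---|---|---|
| 5% | 7.25% | 2.25 points |
| 15% | 11.75% | 6.75 points |
| 30% | 18.5% | 13.5 points |

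For any marker whose effect is zero off drug, the reported effect under the same assumption is m times the week 18 effect. This is an upper case because it puts all of the loss between weeks 18 and 30. Patients who leave before week 8 add nothing, and those who leave after week 30 carry an off-drug value to week 54. The 50% and 5% are planning rates for Treg response at week 18 and serve here only as a scale.

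**4. Frozen decline.** A patient last seen at week 18 has 36 weeks uncounted at week 54: 36 × 7 / 30.4375 = 8.28 months. At 0.7 points per month this is 0.7 × 8.28 = 5.8 ALSFRS-R points (4.1 at 0.5 and 8.3 at 1.0 per month). The 0.7 is the ΔFS cut in Section 2.5, and the unit is assumed. If 15% of an arm were last seen at week 18, its mean would be too high by 0.15 × 5.8 = 0.87 points. With the same loss in both arms this cancels. If one arm lost 10 percentage points more patients at week 18, the bias between arms would be 0.10 × 5.8 = 0.58 points.

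**5. Primary outcome.** A patient with only a baseline Treg shows no change and is a non-responder. A patient who leaves after a week 8 sample, if one is taken, can be a week 18 responder. The plan has 63 patients "with 1:1:1 allocation in 3 groups of 21 subjects each". With 15% dropout, its own formula gives:

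- all leave before week 8: 0.85 × 50% = 42.5% v 0.85 × 5% = 4.25%, power 77.9% at 21 per arm;
- all carry week 8 values at the planned rates: 50% v 5%, power 88.2% at 21 per arm;
- the plan's 18 per arm with complete data: 81.7%.

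**The case against.** The article condenses a fuller protocol, and a statistical analysis plan may narrow the rule. That would excuse silence. It does not excuse a method that is stated without limits. Nor can the sentence be read as a survival rule because of where it stands: Kaplan–Meier, log-rank and Cox analyses handle incomplete follow-up by censoring, so carrying forward can act only on the measured outcomes.

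Several stronger readings are tempting, and the documents do not support them.

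- *15% dropout means a 15% carry-over of the effect.* The 15% was set for week 18, and the formula needs every loss to fall between weeks 18 and 30.
- *ALSFRS-R is biased by 5.8 points.* That is one patient's uncounted decline, in either arm. It becomes bias between arms only if the amount or timing of loss differs.
- *The primary result is biased in favour of Rapamycin.* Section 2.14 takes Treg from baseline and week 18. A week 8 Treg sample is inferred from the cell-subpopulation visits, and the visit table is not available. Even with that sample, the direction depends on when patients leave.
- *The rule undermines the sample size.* Exact Fisher power of 72.9% (21 per arm, 42.5% v 4.25%) set against the planned 80% mixes two tests. Fisher power is already 74.5% at 18 per arm with complete data, so like for like the loss is 1.6 points. By the plan's formula it is 3.8 points (81.7% to 77.9%).

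It is also fair to say that the clinical scales are secondary, that clinical efficacy is left to a later trial, and that Section 2.14 names no test for them. These points limit the weight of the finding, but they do not make the rule suitable.

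**Conclusion.** The concern holds for the off-drug visits and the clinical scales. Followed as written, the rule records end-of-treatment values as off-drug results for patients lost or dead between weeks 18 and 30. Whenever the effect fades, this pushes the persistence question toward yes, and it needs no difference in loss between arms to do so. The size is at most m × 45 points on the planning rates, where m is not given in the article.

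For ALSFRS-R, FVC and ALSAQ-40 the rule hides decline, and it biases the comparison to the extent that loss differs by arm. For the primary outcome the defect is narrower: if Treg is sampled at week 8, response status depends on when a patient leaves, in a direction that cannot be foreseen. The sample size is not called into question.

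**What to change.** Rewrite the missing-data paragraph of Section 2.14 as follows.

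- Replace last observation carried forward and the repeated measures ANOVA with a likelihood-based mixed model for repeated measures on all observed Treg, marker, ALSFRS-R, FVC and ALSAQ-40 values. Specify arm-by-visit contrasts at week 18 and, separately, at weeks 30 and 54.
- State that no on-drug value is carried into weeks 30 or 54.
- Add a joint-rank sensitivity analysis of ALSFRS-R with death or tracheostomy.
- Set one rule for a missing week 18 Treg in the responder analysis, the same whatever the time of leaving: for example non-response, with a sensitivity analysis under another assumption.

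The change needs no new patients, visits or samples, only slightly more analysis work. Precision may look a little worse, because carried values no longer count as data. The non-response rule has its own price: with 15% missing, power by the plan's formula is about 78% at 21 per arm. That is the same dilution as when every dropout carries a baseline value. The gain is that response status no longer depends on when a patient leaves.

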### Outcomes

2.9

The primary outcome is represented by the change from baseline to week 18 in Treg number in ALS patients treated with Rapamycin compared with the control arm.

Secondary outcomes are as follows:

1.*Safety*: Occurrence of AEs and per-treatment arising changes in physical examination, vital signs (blood pressure, pulse rate, and body temperature), body weight, and clinical laboratory tests (biochemistry, hematology). MedDRA dictionary is going to be used for reporting.2.*Rapamycin levels in CSF* at week 18 (high-performance liquid chromatography (HPLC) with mass spectrometry (MS) (LC–MS/MS).3.Change from baseline to each time point (weeks 8, 18, 30, and 54) of the phosphorylation of the S6 ribosomal protein *(S6RP)* comparing Rapamycin arms and placebo arm.4.Change from baseline to each time point (week 8, 18, 30, and 54) of the activation and homing capabilities of different *T, B, NK cell subpopulations* comparing Rapamycin arms and placebo arm.5.Changes from baseline to each time point (weeks 8, 18, 30, and 54) in different *biomarkers* (including peripheral and CSF biomarkers that is, creatinine and albumin, CK, vitamin D, plasma/CSF neurofilament heavy/light chain protein) comparing Rapamycin arms and placebo arm.6.Changes from baseline to each time point (weeks 8, 18, 30, and 54) in *inflammatory status (molecular analysis of the inflammasome system)* comparing Rapamycin arms and placebo arm.7.Change from baseline to each time point (weeks 4, 8, 12, 18, 30, 42, and 54) of *ALSFRS-R.*8.*Survival* defined as the time from randomization to the date of documented death or tracheotomy.9.Survival rate at weeks 18, 36, and 54.10.*Change of FVC* from baseline to each time point (weeks 4, 8, 12, 18, 30, 42, and 54).11.Absolute and relative change from baseline in *ALSAQ-40* (Amyotrophic Lateral Sclerosis Specific Assessment Questionnaire at weeks 4, 8, 12, 18, 30, 42, and 54).

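### Repeated measures ANOVA with last observation carried forward across the end of treatment can falsely suggest that secondary biomarker effects persist off drug

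*Protocol article*

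**What the plan says.** Treatment lasts 18 weeks. The section Treatment and blindness continues: "After treatment end (week 18) patients will be followed up for further 36 weeks". One stated aim of that period is to learn whether biological or clinical effects outlast the drug.

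The Outcomes section asks for results visit by visit, for example "Change from baseline to each time point (weeks 8, 18, 30, and 54) of the phosphorylation of the S6 ribosomal protein". Cell subpopulations, other biomarkers and the inflammasome have the same four visits. Two fall during or at the end of treatment (weeks 8 and 18). Two fall 12 and 36 weeks after it (30 − 18 = 12; 54 − 18 = 36).

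The Statistical analyses section plans two analyses of these variables:

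- a comparison of the change from baseline to week 18 between Rapamycin and placebo, by t test or Wilcoxon–Mann–Whitney test;
- an analysis of mean change over time, which "will be assessed using repeated measures ANOVA, with treatment as between-subjects factor and time as within-subjects factor".

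The same section names LOCF as the rule for missing data, without limiting it to particular outcomes or visits. It does not say which ANOVA term will be read, or which visits enter the model.

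**The concern.** The on-drug question (does Rapamycin change the biomarker?) and the off-drug question (does the change last?) are different, and the protocol asks both. The first has its own week-18 test. The second rests entirely on the repeated measures ANOVA, because no other listed biomarker analysis reaches past week 18.

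Classical repeated measures ANOVA needs a value at every visit for every patient, and LOCF supplies the missing ones. For a patient lost after week 18, the value supplied at weeks 30 and 54 was measured at the end of treatment. It is entered as an off-drug measurement although it is not one. Loss is foreseeable here: death or tracheotomy is itself an outcome, with survival rates reported to week 54.

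At stake is a false signal that a biomarker effect persists after stopping, in a trial whose stated purpose is to inform a later efficacy trial. In addition, the overall ANOVA tests do not give the per-visit changes that the Outcomes section defines.

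**Working it through.** **1. The plan's own figure.** The article gives a sample size for the primary responder comparison only. The inputs are "≥50% of treated patients compared with a maximum 5% of patients in the placebo group" and "alpha error of 0.025 (to take into account a multiple comparison with a control arm) and a power of 0.80". With the pooled-variance formula and a two-sided 0.025:

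n = [2.241·√(2·0.275·0.725) + 0.842·√(0.5·0.5 + 0.05·0.95)]² / 0.45² = 17.4, so 18 per arm and 3 × 18 = 54.

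This reproduces the stated 54. Adding 15% gives 54 × 1.15 = 62.1, rounded up to 63, or 21 per arm. There is no corresponding figure for the ANOVA. Biomarker effect size, correlation, degree of wash-out and loss after week 18 are not given, so all of them are assumed below.

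**2. What LOCF does to the off-drug visits.** Let d be the active-minus-placebo difference at week 18, and r the share of it that truly remains at a later visit. Let f be the fraction of active-arm patients whose later value is filled from week 18. Assume that filled patients have the average effect and that the same fraction is filled on placebo. Then

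estimated difference = (1 − f)·r·d + f·d, so bias = f·(1 − r)·d.

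| True share remaining, r | Bias, f = 15% | Bias, f = 30% |
|---|---|---|
| 0 (full wash-out) | 0.15 d | 0.30 d |
| 0.5 | 0.075 d | 0.15 d |
| 1 (full persistence) | 0 | 0 |

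With 21 per arm, 15% and 30% are about 3 and 6 patients. The bias is always towards persistence and is largest when there is none. Values carried from week 8 act the same way, with the week-8 effect in place of d. A carried baseline value adds nothing under wash-out and pulls a lasting effect down.

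If the fractions filled differ (fA active, fP placebo) and the untreated level drifts by D after week 18, the estimate under full wash-out is fA·d − (fA − fP)·D. Unequal loss therefore adds a second error of either sign.

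**3. What the overall ANOVA terms can show.** Under full wash-out, the treatment main effect averages (d + d + 0 + 0)/4 = 0.5 d over the four post-baseline visits. If baseline is a fifth time level, it averages (0 + d + d + 0 + 0)/5 = 0.4 d.

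A simulation shows how often each term is significant. It assumes one active arm against placebo, 21 per arm, an on-drug effect of 0.8 SD, equal correlation of 0.5 between visits, complete data, two-sided 0.05 and 4,000 runs. Baseline is a time level for the raw main effect and the interaction.

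| Effect after week 18 | Main effect, raw | Main effect, mean change | Treatment-by-time | Planned week-18 t test |
|---|---|---|---|---|
| none | 25% | 37% | 91% | 73% |
| half | 49% | 69% | 68% | 73% |
| full | 75% | 89% | 75% | 73% |

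The interaction is often significant whether the effect vanishes, halves or lasts, so a significant result does not say which happened. The main effect depends on persistence but blends it with the on-drug effect. If change scores at the four post-baseline visits were modelled instead, the interaction would test whether the effect varies between visits. A non-significant result would still not demonstrate persistence, and no estimate at weeks 30 or 54 would follow from it. The week-18 t test is unaffected by what happens afterwards.

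**The case against.** A reader might infer that the ANOVA dilutes a real on-drug effect so that the trial misses it. The documents do not support that, for three reasons. The week-18 comparison of the same variables is planned just before the ANOVA and does not use weeks 30 and 54. The article never says that the treatment main effect is the term to be read; for change over time, treatment-by-time is the natural term, and it is not diluted. The halving also requires that the effect fade, and with full persistence averaging costs nothing.

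It can also be said that an article may leave the tested term and the contrasts to a fuller plan. That is fair, and silence on the tested term is not the point here. Visit-specific contrasts could be drawn from a two-factor ANOVA as well, but contrasts at weeks 30 and 54 computed from carried-forward data would keep the bias shown above.

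The LOCF sentence stands beside the survival methods, so it might be read as limited to them. But it carries no such limit, and carrying a value forward has no evident role in a Kaplan–Meier or log-rank analysis. It fits repeated measurements such as these.

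Finally, these are secondary outcomes, and the primary Treg analysis uses baseline and week 18 only. That stands and limits the weight of the point.

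**Conclusion.** The concern holds in a limited form. The stated combination of repeated measures ANOVA and LOCF spans the end of treatment, and it is the only listed biomarker analysis able to address persistence. Under full wash-out it leaves a spurious residual of f times the week-18 effect, or 15% to 30% of that effect for f of 15% to 30%. The bias shrinks in proportion to true persistence and is zero if the effect lasts fully. The fraction f is an assumption. The protocol's 15% drop-out belongs to the sample size for the week-18 endpoint and does not estimate loss by week 54.

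Neither overall ANOVA term separates on-drug effect from persistence. The simulated percentages illustrate this under assumed effect, correlation and wash-out, and they do not predict this trial's power. The documents do not support going further and saying that target engagement would be missed, because the week-18 comparison tests it directly. The point affects interpretation of secondary biomarkers at weeks 30 and 54. It should be corrected, but it does not threaten the primary analysis.

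**What to change.** Replace the repeated measures ANOVA with LOCF by a mixed model for repeated measures on all observed values at weeks 8, 18, 30 and 54. Include arm (three levels), visit, arm-by-visit, baseline value and the ΔFS stratum. An unstructured covariance over four visits needs 4 × 5/2 = 10 parameters.

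Report each dose against placebo at week 18 as the on-treatment contrast. Report the contrasts at weeks 30 and 54 separately as the persistence results, with estimates and confidence intervals. Do not carry values forward, and do not impute data after death.

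The cost is revised wording and slightly more analysis work, with no new data or visits. The downside is reliance on a missing-at-random assumption, which is open to question where patients leave because they are progressing. The number of patients observed at each visit, by arm, should accompany the estimates.
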